## Methods

### Aims

The primary aim of the study is to assess patient’s pain scores for the first 10 days post procedure using a visual analogue scale (VAS). Secondary aims are to compare the two treatment groups with respect to: quality of life scores at baseline, 2 weeks and 6 months using the EQ-5D (EuroQol 5 Dimensions), AVVQ (Aberdeen Varicose Vein Questionnaire) and CIVIQ (ChronIc Venous Insufficiency quality of life Questionnaire) scores; clinical change using the VCSS (Venous Clinical Severity Score) at baseline, 2 weeks and 6 months; the degree of bruising (mild, moderate and severe) and phlebitis at 2 weeks and 6 months; patient compliance with the intervention; time taken to return to work and normal activities; patient satisfaction, assessed with a patient satisfaction questionnaire; and successful obliteration of the target vein, assessed with duplex ultrasound scan at 6 weeks and 6 months. Recanalisation will be defined by a segment of vein ≥ 5 cm. A comparison of the cost-effectiveness of the intervention will also be carried out.

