### Statistical analysis

All analysis will be undertaken on an intention-to-treat basis. Pain score data will be treated as non-parametric and compared using the Mann–Whitney *U* test. Multivariable predictors for higher VAS pain scores will be determined using linear/non-linear regression. Other continuous data will be compared by the Student *t* test or Mann–Whitney *U* test for parametric and non-parametric data, as appropriate. The median and first and third quartiles will be reported for continuous variables. Categorical data will be compared by the chi-square test or Fisher’s exact test, as appropriate, with a *P* value less than 0.05 indicating significance. The 5% level will be considered significant throughout. The individual undertaking the analyses will be blinded to trial allocation.

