## Discussion

The role of compression following endovenous interventions for superficial venous reflux remains unclear. If indicated, the optimal duration of treatment is also obscure. Non-tumescent, non-thermal (NTNT) endovenous techniques are increasingly used as they facilitate a more office-based approach to venous interventions. The COMMOCA trial will provide valuable data regarding the role of compression as an adjunct to one of the NTNT techniques. The primary aim of the study is to assess patient’s pain scores for the first 10 days post procedure using a visual analogue scale. Secondary aims include an assessment of patient compliance with compression, quality of life scores, clinical effectiveness, rates of bruising and phlebitis, time taken to return to normal activities, patient satisfaction and occlusion rate at 6 months.

This trial has some potential weaknesses, including the simple randomisation technique which has been chosen. This may lead to issues such as the production of unequal sample sizes. Additionally, the potential for losses to follow-up is a weakness in any trial of venous interventions. Short-term outcomes such as pain score are relatively straightforward to capture. However, early recurrence and recanalisation rates are of major concern to interventionists and require longer follow-up. COMMOCA is set in two established ambulatory venous centres with pathways for follow-up already in place. Between them, the two centres undertake over 1000 superficial venous procedures per annum. Six-month follow-up completion rates will be monitored closely throughout the trial. If necessary, the sample size will be recalculated to reflect a greater than expected drop-out rate and ensure sufficient statistical power regarding recanalisation rates at the end of the trial.

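### The 5% level is declared significant for every comparison, although about 9 to 17 secondary between-arm comparisons are listed without ranking or a supportive label

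*Protocol article*

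**What the plan says.** The Aims section names one primary aim, pain on a visual analogue scale over the first 10 days. It then frames the remaining outcomes as comparisons between the arms: "Secondary aims are to compare the two treatment groups with respect to" a list that begins with "quality of life scores at baseline, 2 weeks and 6 months using the EQ-5D (EuroQol 5 Dimensions), AVVQ (Aberdeen Varicose Vein Questionnaire) and CIVIQ". The list goes on to VCSS at the same three times, bruising and phlebitis at two visits, compliance, return to work and to normal activities, satisfaction, and obliteration of the vein at two scans. A cost-effectiveness comparison is added.

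The Statistical analysis section assigns tests by type of variable. For non-pain continuous outcomes: "Other continuous data will be compared by the Student" t test or the Mann–Whitney test. For categorical outcomes, chi-square or Fisher's exact test is used with a P "value less than 0.05 indicating significance". It also plans a regression: "Multivariable predictors for higher VAS pain scores will be determined using linear/non-linear regression". The rule that covers all of this is "The 5% level will be considered significant throughout".

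The article contains no ranking of the secondary outcomes, no division of alpha, no condition on the primary result, and no statement that the secondaries are supportive or exploratory.

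**The concern.** An unseen analysis plan may well handle multiplicity, and silence in a condensed article would be no finding. Here the article is not silent. It fixes a decision rule and extends it to every comparison, so on the plain reading each secondary P value below 0.05 is a significant result.

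The secondaries cover quality of life, clinical severity, bruising, phlebitis, recovery time, satisfaction and occlusion. The trial is meant to clarify whether compression has a role after this procedure. If the pain comparison were null, one chance result somewhere in that list could be reported, in full agreement with the written plan, as significant evidence for or against stockings.

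The Aims section also names baseline among the times at which quality of life and VCSS are compared. If these were tested, any baseline difference between randomised arms would be due to chance, so the test would answer no useful question.

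**Working it through.** **No stated figure to reproduce.** The article gives no error rate for the secondary family. The check is therefore a count of comparisons and the error rate that follows from it.

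**Count of post-baseline between-arm comparisons (Aims section), all listed times**
- EQ-5D, AVVQ, CIVIQ at 2 weeks and 6 months: 3 × 2 = 6
- VCSS at 2 weeks and 6 months: 2
- Bruising and phlebitis at 2 weeks and 6 months: 2 × 2 = 4
- Return to work, return to normal activities: 2
- Satisfaction: 1
- Obliteration at two scans: 2

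Total: 6 + 2 + 4 + 2 + 1 + 2 = 17.

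Not counted: compliance (group B receives no stockings, so there is nothing to compare), cost-effectiveness, the regression of predictors of pain, and baseline comparisons.

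**Other defensible counts**
- The Follow-up section does not list bruising or phlebitis at 6 months. Dropping them gives 17 − 2 = 15.
- One time point per outcome gives 4 scales + 2 (bruising, phlebitis) + 1 (return to activities or work) + 1 (satisfaction) + 1 (obliteration) = 9. It is 10 if the two return times stay separate.
- The first scan is at 6 weeks in the Aims and at the 2-week visit in the Follow-up section. The two should be reconciled, but the count of scans stays at 2.

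**Error rate.** Assumptions: all null hypotheses true, and each test two-sided with exactly 5% error (the article does not state sidedness).
- Expected number of false positives, at any correlation: 17 × 0.05 = 0.85; 9 × 0.05 = 0.45.
- Independent tests: 1 − 0.95^k. For k = 17: 1 − 0.418 = 0.582. For k = 15: 0.537. For k = 9: 0.370.
- Correlated tests: 1 − P(all |Z| < 1.96) for normal test statistics with common correlation ρ, by numerical integration. The documents give no correlation, so ρ is an assumption and a range is shown.

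| Tests | ρ = 0 | ρ = 0.3 | ρ = 0.5 | ρ = 0.8 |
|---|---|---|---|---|
| 17 | 58% | 49% | 39% | 21% |
| 15 | 54% | 46% | 36% | 20% |
| 9 | 37% | 33% | 27% | 17% |

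With 10 tests instead of 9 the independent figure is 1 − 0.95^10 = 40%.

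For 17 tests the chance falls below 50% once ρ exceeds about 0.28. A simulation with higher correlation within outcome domains than between them gave 54% (within 0.3, between 0.1), 42% (0.7, 0.2) and 36% (0.8, 0.3).

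**The case against.** The strongest reply is that the main safeguard is already present. One primary aim is named, the rest are labelled secondary, and testing secondaries at a nominal 5% is common in a two-arm trial of this kind. The label warns the reader, and no sentence says that a positive secondary would be claimed as proof. This stands in part: the harm depends on how the results are reported. But the article never says that the secondaries will be read as supportive, and it does attach the word significant to each of them.

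The count can also be disputed. The Aims section lists assessment times, not tests, and Fisher's exact test is conservative with sparse events, so a full 5% per categorical test is an upper bound. Both points stand, which is why the count is given as a range and the figures as approximate.

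Adjusted P values read at 5% would also be compatible with the sentence. That is possible, but the plain reading is unadjusted testing.

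Three stronger readings are tempting, and the documents do not support them:
- A reader might infer that a false secondary finding is likely. Better than even odds with 17 tests need a correlation below about 0.28, and three quality of life scales and VCSS, each measured twice, may well be more correlated than that.
- A reader might compare these rates with the stated 5% and say that the plan exceeds its own limit several times over. The stated 5% is a per-test level; no family-wise rate is promised.
- The Discussion says that the sample size may be recalculated to "ensure sufficient statistical power regarding recanalisation rates at the end of the trial". A reader might infer confirmatory status for recanalisation. Wanting adequate power for an outcome does not confer that status, and the same section lists occlusion at 6 months among the secondary aims.

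**Conclusion.** The point holds as a weakness in a stated rule. The article calls any comparison below 0.05 significant while listing about 9 to 17 secondary between-arm comparisons with no order and no supportive label. With all nulls true, the chance of at least one nominally significant secondary is 58% for 17 independent tests and about 21% to 49% at correlations of 0.8 to 0.3. For 9 tests it is about 17% to 37% over correlations of 0.8 to 0. These figures rest on an assumed correlation, two-sided testing and exact 5% error per test.

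The error rate of the primary pain comparison is not affected, and nothing here bears on sample size or conduct. What is affected is what the trial may claim from its secondaries, above all if pain shows no difference. Correction is worthwhile because it is cheap and recruitment has not begun.

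**What to change.** Replace the sentence on the 5% level in the Statistical analysis section with:

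> The two-sided 5% level applies to the primary pain comparison. Secondary comparisons and the regression of predictors of pain are supportive; they are reported as effect estimates with 95% confidence intervals, unadjusted for multiplicity, and an isolated P < 0.05 is not taken as proof of an effect.

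The clause on categorical data that sets its own 0.05 threshold should be brought into line. Report baseline quality of life and VCSS descriptively, without between-arm tests.

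Formal alpha adjustment of all secondaries is not needed. If the sponsor wants a confirmatory claim on one secondary, such as recanalisation at 6 months, it can name that outcome and test it at 5% only if the primary comparison is significant.

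The cost is one or two sentences before recruitment, with no extra patients or data. The downside is that an isolated secondary P below 0.05 can no longer be presented as a significant finding.

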### Data handling and dissemination of results

All patient data will be anonymised and stored on a password-protected access database. Patient records will be kept on paper in the form of the diary card questionnaires and clinical scoring sheets. These will be kept in a locked filling cabinet at each trial site.

### Criteria for electively stopping the trial or other research prematurely

The trial may be stopped prematurely due to loss of equipoise or any major adverse effect as a result of treatment in any of the treatment arms.

### Adverse events and serious adverse events

No significant adverse events are expected. An adverse event (AE) is defined as any untoward medical occurrence in a patient or clinical study subject. A serious adverse event (SAE) is any untoward and unexpected medical occurrence or effect that results in death or is life-threatening (refers to an event in which the subject was at risk of death at the time of the event). It does not refer to an event which hypothetically might have caused death if it was more severe, requires hospitalisation or prolongation of existing inpatients’ hospitalisation, results in persistent or significant disability or incapacity, or is a congenital anomaly or birth defect.

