### Reporting procedures

All adverse events should be reported. Depending on the nature of the event, the reporting procedures should be adhered to; any questions concerning adverse event reporting should be directed to the Chief Investigator in the first instance.

All AEs, whether expected or not, should be recorded. In the case of SAEs, a SAE form should be completed and faxed to the Chief Investigator within 24 h. All SAEs should be reported to the Research Ethical Committee when, in the opinion of the Chief Investigator, the event was ‘related’ (i.e. resulted from the administration of any of the research procedures) and ‘unexpected’ (i.e. an event that is not listed in the protocol as an expected occurrence). Reports of related and unexpected SAEs should be submitted within 15 days of the Chief Investigator becoming aware of the event, using the NRES (National Research Ethics Service) SAE form for non-investigational medicinal product studies. Local investigators should report any SAEs as required by their Local Research Ethics Committee, Sponsor and/or Research & Development Office.

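### As punctuated, the SAE definition leaves out hospitalisation, disability and congenital anomaly and requires unexpectedness, so some serious events would miss the 24 h and 15-day reporting routes

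*Protocol article*

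**What the plan says.** In the protocol article, under Adverse events and serious adverse events, the definition reads: "A serious adverse event (SAE) is any untoward and unexpected medical occurrence or effect that results in death or is life-threatening". A bracketed explanation of life-threatening follows, and the sentence closes. The next sentence starts "It does not refer to an event which hypothetically might have caused death if it was more severe, requires hospitalisation or prolongation of existing" inpatient stays, and the same sentence ends "results in persistent or significant disability or incapacity, or is a congenital anomaly or birth defect". The section also states that no significant adverse events are anticipated.

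Under Reporting procedures, the expedited route depends on the SAE label: "In the case of SAEs, a SAE form should be completed and faxed to the Chief Investigator within 24 h". SAEs that the Chief Investigator judges both related and unexpected go to the ethics committee, with a report due within 15 days of the Chief Investigator learning of the event. Unexpected is defined there as not being listed in the protocol as an expected occurrence. Local investigators also report SAEs as their own committee, sponsor or research office requires. Two rules cover everything else: "All adverse events should be reported" and "All AEs, whether expected or not, should be recorded". Neither carries a time limit.

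**The concern.** A clarification that belongs to one criterion (life-threatening) has become the opening of the sentence that holds the remaining criteria. The negation at its start then covers hospitalisation, disability and congenital anomaly. Separately, seriousness and expectedness are mixed: the definition requires an event to be unexpected before it can be serious, and the reporting section then asks again whether it is unexpected.

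At stake is the sorting of events into the timed reporting routes. The SAE label decides whether the Chief Investigator hears within 24 h and whether the 15-day ethics report can apply. The trial runs at two hospitals in two countries. If one site follows the literal text and the other the evident intention, the same event could be handled differently.

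**Working it through.** No arithmetic beyond a count applies; the check sets the two sections against each other.

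**Step 1: criteria named in the definition, as punctuated.**

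| Criterion | Position in the text | SAE on the literal reading? |
|---|---|---|
| Death | Defining sentence | Yes, if unexpected |
| Life-threatening | Defining sentence | Yes, if unexpected |
| Hospitalisation or its prolongation | Sentence opening with the negation | No |
| Persistent or significant disability or incapacity | Same sentence | No |
| Congenital anomaly or birth defect | Same sentence | No |

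Two of the five criteria are affirmed and three are negated (2 + 3 = 5).

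**Step 2: does the reading depend on what the opening pronoun refers to?** If it stands for the SAE, the three criteria are excluded outright. If it stands for the term life-threatening, they are described as things that term does not cover, and they still appear nowhere as SAE criteria. Only by treating the later verbs as a continuation of the previous sentence does the full list return. That is very likely what was meant, because those verbs run parallel to the ones used for death and life-threatening, but the punctuation does not say it.

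**Step 3: the role of unexpected.** By the definition, every SAE is unexpected. The ethics-committee route selects SAEs that are related and unexpected. If all SAEs are already unexpected, that selection reduces to SAEs that are related, and the second condition does nothing. The reporting section therefore presupposes that an SAE can be expected, while the definition says it cannot.

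**Step 4: follow one event through.** Take a related admission to hospital that is not life-threatening. The section on technique gives heparin after the procedure to lower the risk of deep vein thrombosis, so a complication of this kind is within the protocol's own view.

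- Adverse event: yes. It is recorded and reported, with no stated deadline.
- SAE: no, on the literal reading.
- 24 h form to the Chief Investigator: not triggered.
- 15-day ethics report: not triggered, because that route selects from SAEs.
- Local reporting: depends on local requirements, which the article does not give.

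What is lost is the classification and the deadline, not the record of the event.

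**The case against.** The strongest reply is that this is a slip of punctuation whose intended meaning any experienced site would recover. The parallel verbs support that. The article also cites Study Protocol Version 1.4, which is not shown; the slip may be absent there and on the SAE form that sites complete. This is fair as to cause and limits what can be said about practice. It does not remove the point: the article sets out the definition in full, and a safety definition should not depend on readers reversing its literal sense.

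Several stronger readings are tempting, and the documents do not support them.

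- *Most serious harms would escape reporting.* Three of five is a count of criteria, not of events. No SAE rates are given, and congenital anomaly has little bearing here because pregnancy is an exclusion.
- *Safety data would be under-collected.* All adverse events must be recorded and reported, so the events remain in the data.
- *A comparison of SAEs between arms would be compromised.* Neither the aims nor the statistical analysis section plans one.
- *The stopping rule would fail.* It refers to a major adverse effect of treatment and does not use the SAE definition. Prompt reporting would help it, but the text makes no direct link.
- *Requiring unexpectedness removes many events.* The article lists no expected occurrences and anticipates no significant ones, so the set removed has no identified members. The fault is the mismatch with the reporting section.

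**Conclusion.** The definition is wrong as written. On its literal reading, SAEs are confined to unexpected events that are fatal or life-threatening, and three of the section's own five criteria are negated. A non-life-threatening admission or a disabling event would be captured as an adverse event but would bypass the 24 h form and the 15-day ethics-committee route. The expectedness condition in the definition also makes the later expectedness test redundant, so the two sections need to be reconciled.

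The number of events affected cannot be estimated from the documents. The conclusion assumes that sites work from the text as the article prints it. This is an error in an operative safety definition, worth correcting before the first patient. It ranks below faults that threaten the trial's main result: the 10-day pain outcome, randomisation, sample size and analysis are untouched.

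**What to change.** Rewrite the definition using only the criteria already in the section. An SAE would be any untoward medical occurrence or effect meeting at least one of the following:

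- (a) it results in death;
- (b) it is life-threatening;
- (c) it requires admission to hospital or prolongs an existing stay;
- (d) it causes lasting or significant disability or incapacity;
- (e) it is a congenital anomaly or birth defect.

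Place the explanation of risk of death at the time of the event, and the clause on events that might hypothetically have been fatal, under (b) only. Remove the requirement of unexpectedness from the definition, and leave relatedness and expectedness to the Reporting procedures section. Then check that the full protocol and the SAE form carry the same wording.

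The cost is a one-paragraph correction, made while recruitment has not yet started, and possibly a few additional SAE forms. No change to the design or the analysis follows.

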### Reporting procedures

All adverse events should be reported. Depending on the nature of the event, the reporting procedures should be adhered to; any questions concerning adverse event reporting should be directed to the Chief Investigator in the first instance.

All AEs, whether expected or not, should be recorded. In the case of SAEs, a SAE form should be completed and faxed to the Chief Investigator within 24 h. All SAEs should be reported to the Research Ethical Committee when, in the opinion of the Chief Investigator, the event was ‘related’ (i.e. resulted from the administration of any of the research procedures) and ‘unexpected’ (i.e. an event that is not listed in the protocol as an expected occurrence). Reports of related and unexpected SAEs should be submitted within 15 days of the Chief Investigator becoming aware of the event, using the NRES (National Research Ethics Service) SAE form for non-investigational medicinal product studies. Local investigators should report any SAEs as required by their Local Research Ethics Committee, Sponsor and/or Research & Development Office.

